##### Economic evaluation measures

The EuroQol-5 Dimension-5 Level (EQ-5D-5L) questionnaire [80] compiles a composite score (i.e., health state utility value) from ratings of perceived health across five domains: (1) mobility; (2) self-care; (3) usual activities; (4) pain/discomfort; and (5) anxiety/depression. A health resource utilization questionnaire will quantify health care system-related costs during the study period [81].

##### Blood and saliva samples

In a subset of participants who consent, fasting blood samples will be collected in the morning by standard venipuncture at baseline, 6, and 12 months. Blood will be processed and stored at – 80 °C as plasma, serum, and whole blood. The main analytes of interest include pro and mature BDNF, IGF-1, VEGF, Cathepsin-B, irisin, adiponectin, sex steroid hormones (estradiol, estrone, testosterone), s100-B, and pro- and anti-inflammatory cytokines (e.g., IFN-γ, IL-1β, IL-4, IL-6, IL-10, IL-12p70, IL-13, IL-17, TNF-α, Rantes, CXCL1, IL-18, TGF-β). To examine potential genetic moderation of exercise efficacy, we will examine the BDNF Val66Met polymorphism, a common single-nucleotide polymorphism within the pro-domain region of the human BDNF gene resulting in an amino acid substitution of valine (Val) to methionine (Met) at position 66. We will also obtain the apolipoprotein E genotype. DNA will be extracted from whole blood by standard protocol and genotype will be determined by a TaqMan by-design assay. Remaining blood samples will be stored for future analyses.

In a subset of participants who consent, saliva samples will be taken to assess hypothalamic–pituitary–adrenal axis activity. Specifically, we will examine: (1) total cortisol concentration over the day (area under the curve); (2) cortisol awakening response, a distinct aspect of the circadian cortisol profile; and (3) changes in cortisol response to engaging in an exercise class with time of day held constant. Free cortisol levels will be assessed in salivary samples (Salivette®) collected 5× each day (at awakening, 30 min after awakening, 2 pm, 4 pm, and bedtime) for 2 consecutive days at each measurement point. Also, salivary samples will be collected immediately before and immediately after the first exercise class and the last exercise class to examine cortisol response to exercise.

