##### Allocation concealment

Participant recruitment and enrollment will be managed by research personnel who will screen for eligibility, acquire consent, and conduct baseline assessments. Randomization to an intervention group will occur after completion of the baseline assessments. Research personnel conducting assessments and data analysis will be blinded to group allocation so unblinding will not occur. We will not be able to blind participants or personnel delivering the interventions and obtaining the monthly physical activity data (see intervention compliance). Blinding will be supported by providing explicit instructions to the research personnel and participants not to discuss issues related to physical activity during the assessments.

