##### Progressive resistance training

The PRT program will consist of a combination of free weight exercises including mini-squats, mini-lunges, and lunge walks and pressurized air system exercises including biceps curls, seated row, latissimus dorsi pull downs, triceps extension, leg press, hamstring curls, and calf raises. The intensity of training will begin at 50–60% of their 1 repetition maximum (1RM) and progress to 2 sets of 6–8 repetitions at 75–85% 1RM by week 4. The 7RM method will be used to increase the training load when 2 sets of 6–8 repetitions are completed with the correct form. The number of sets completed and the load lifted will be recorded for each participant at each class.

To meet the public health mandates of COVID-19, when it is necessary, training will occur at home, with the use of resistance bands of various weights. Participants will be provided access to instructional videos by either YouTube or DVD. They will be called on a weekly basis to monitor progress and compliance.

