### Statistical analyses

The analyses will follow the intention-to-treat principle (i.e., all individuals will be analyzed according to their group allocation regardless of compliance). We will evaluate between-group differences (PRT vs. BAT) in ADAS-Cog-Plus and WMH volume, adjusted for baseline score, using mixed linear models. Restricted maximum likelihood estimation will be used in order to include all randomized participants to estimate treatment effects, regardless of loss to follow-up. Time since baseline (6 months versus 12 months) will be considered as a repeated variable and will be included as a fixed effect in addition to group and group-by-time interaction. Baseline score on the outcome variable and participant baseline characteristics will be included as fixed covariates. The intercept will be specified as a random effect. Primary and secondary outcomes will be analyzed using this same analytic model.

The intention-to-treat analysis will be followed by a complete-case analysis, in which only participants with valid data at all time points will be included. Moreover, we will compare participants in the PRT group who are compliant with the intervention (defined as attending at least 60% of the total exercise sessions) with the BAT group.

To explore underlying mechanisms, we will assess the association between changes in cognitive function with changes in: (1) neuroimaging outcomes; (2) cardiometabolic risk factors; (3) blood biomarkers; and (4) saliva biomarkers.

The economic evaluation will examine the efficiency of the 12-month PRT program compared with BAT. The outcome of our cost–utility analysis is the incremental cost–utility ratio (ICUR): ICUR = ∆Cost/∆ quality-adjusted life years (QALYs); QALYs, estimated from the EQ-5D-5L, represent time spent in given health states [85, 86].

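### The cortisol response to a class has no pre-randomisation value, so the common baseline-adjusted model estimates neither the last-class arm difference nor the arm difference in change

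*Protocol article*

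**What the plan says.** All references are to the protocol article.

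- **Outcome.** Under Secondary outcomes, Blood and saliva samples lists three cortisol measures for a consenting subset: total concentration over the day, the awakening response, and "changes in cortisol response to engaging in an exercise class with time of day held constant".
- **Sampling.** For the third measure, "salivary samples will be collected immediately before and immediately after the first exercise class and the last exercise class". The diurnal samples behind the first two are taken "for 2 consecutive days at each measurement point", so those two have a true baseline. They do not measure the response to a class.
- **Order of events.** Allocation concealment states: "Randomization to an intervention group will occur after completion of the baseline assessments".
- **What happens in class.** In the Progressive resistance training (PRT) section, "The intensity of training will begin at 50–60% of their 1 repetition maximum", rising to 75–85% by week 4. The Balance and tone training (BAT) section describes stretching, core work, breathing and relaxation, with no load beyond body weight.
- **Analysis.** Statistical analyses states: "Baseline score on the outcome variable and participant baseline characteristics will be included as fixed covariates". It then sets the scope: "Primary and secondary outcomes will be analyzed using this same analytic model". No exception is made for the class-response measure.

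**The concern.** Baseline adjustment in a randomised trial is safe because the covariate is fixed before allocation and so cannot be affected by it. The class-response measure has no such value. Classes belong to the assigned programme, so the first class comes after randomisation, and in it one arm lifts loads while the other does not. If the two kinds of session provoke different acute cortisol responses, the first-class value already carries part of the effect of allocation.

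The blanket rule still asks for a baseline score for this outcome, and the first-class response is the only candidate. The resulting arm coefficient would be reported as the effect of PRT on cortisol response, yet it would not be the difference between arms at the last class, nor the difference between arms in how the response changed.

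**Working it through.** The article gives no cortisol effect, SD or correlation, so there is no figure of its own to reproduce. The check is algebra with assumed inputs, confirmed by simulation.

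**Definitions**, in SD units, with equal SDs at both classes:
- d1 = PRT minus BAT difference in the pre-to-post response at the first class
- d2 = the same difference at the last class
- rho = within-arm correlation between a person's first-class and last-class responses

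**What each analysis estimates**
- Last-class difference, either unadjusted or adjusted for a genuine pre-randomisation covariate: d2.
- Difference in first-to-last change: d2 − d1.
- Last-class response adjusted for the first-class response: the within-arm slope is rho, and the arms differ by d1 on the covariate, so the arm coefficient is d2 − rho×d1.
- Change score adjusted for the first-class response: the slope is rho − 1, so the coefficient is (d2 − d1) − (rho − 1)×d1 = d2 − rho×d1. Using change as the dependent variable while keeping the covariate alters nothing.

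The adjusted coefficient equals d2 only if d1 = 0 or rho = 0. It equals d2 − d1 only if d1 = 0 or rho = 1.

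**Numbers**, with d2 = 0.50 throughout (assumed). The simulation used 400,000 subjects per setting; its result is in brackets.

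| d1 | d2 | d2 − d1 | Adjusted, rho = 0.3 | Adjusted, rho = 0.5 | Adjusted, rho = 0.7 |
|---|---|---|---|---|---|
| 0 | 0.50 | 0.50 | 0.50 (0.497) | 0.50 (0.500) | 0.50 (0.498) |
| 0.25 | 0.50 | 0.25 | 0.425 (0.422) | 0.375 (0.373) | 0.325 (0.326) |
| 0.50 | 0.50 | 0 | 0.35 (0.353) | 0.25 (0.248) | 0.15 (0.153) |

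In the same runs a pre-randomisation covariate gave 0.495 to 0.503, which recovers d2. The plain change score gave 0.497 to 0.501, 0.245 to 0.251 and −0.002 to 0.003 in the three rows, apart from simulation noise matching d2 − d1.

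**Reading the table.** In the last row the adjusted coefficient falls short of the last-class difference by 0.15, 0.25 and 0.35, and exceeds the true difference in change (zero) by 0.35, 0.25 and 0.15. The direction of the error therefore depends on which quantity the reader believes is being estimated. If d1 and d2 had opposite signs, the coefficient would be larger in size than d2.

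**The case against.** The strongest reply is that the article defines this outcome as a change, so the first class is its natural reference and the last-class difference is not the truth to judge the model against. That is right, and it limits what can be claimed. A reader might infer that the model would manufacture a finding that PRT lowers cortisol reactivity. Take d1 = 0.6 and d2 = 0 (assumed): the model returns −0.18, −0.30 and −0.42 for rho = 0.3, 0.5 and 0.7, but the true difference in change is 0 − 0.6 = −0.6. For the outcome as named, the model understates a real difference and does not create one. What stands is that covariate adjustment does not deliver the change contrast either.

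A second reply is that the article never calls the first-class value a baseline score, and that the model's 6-versus-12-month factor does not fit a class-linked outcome, so special handling must have been intended and may sit in an analysis plan not shown. The first half is true: the covariate is inferred, as the only earlier value there is. The second half is weak. The same section applies the model by name to white matter hyperintensity volume, which is scanned only at baseline and 12 months, so the lack of a 6-month value signals no exemption. If the model instead cannot be fitted to this outcome, the wording still needs correcting.

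A reader might also infer that the distorted estimate flows into the mechanism analysis. The article does not support this. That analysis relates changes in cognition to changes in saliva biomarkers, so the adjusted arm coefficient is not an input, and the article does not say which of the three cortisol measures it uses.

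Finally, the article nowhere says that a first-to-last change will be read as adaptation of the stress axis, so it should not be charged with that interpretation.

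**Conclusion.** The point holds in a limited form. Applied as written, the common model adjusts the class-response outcome for a value measured after allocation and under the assigned exercise. It then estimates d2 − rho×d1, which is neither the last-class arm difference nor the arm difference in change that the article names.

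The size is unknown. It rests on an assumed first-class difference, an assumed correlation and equal SDs. Over d1 = 0.25 to 0.50 and rho = 0.3 to 0.7, the coefficient departs from a last-class difference of 0.50 by rho×d1 = 0.075 to 0.35 SD. It departs from the difference in change by (1 − rho)×d1, which over the same range is also 0.075 to 0.35 SD. If the arms respond alike at the first class, there is no distortion.

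This is a minor finding: one of three cortisol measures, in a consenting subset, among many secondary outcomes. The primary outcomes, and the two cortisol measures with a true baseline, are unaffected.

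**What to change.** State in the analysis plan that the cortisol response to a class is exempt from the baseline-adjusted model. Then:

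1. Treat the pre-to-post response at the first and at the last class as two repeated post-randomisation outcomes, with group, class and group-by-class as fixed effects and no first-class covariate.
2. Report the arm difference at each class (d1 and d2), and the group-by-class contrast as the difference in change (d2 − d1). This keeps the outcome that the article names.
3. If a covariate is wanted, use the pre-randomisation diurnal cortisol already collected at the baseline measurement point.
4. When interpreting the change, note that the prescribed PRT load differs between the first and last class while BAT adds none, so the contrast reflects a different stimulus as well as any altered response.

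No new samples are needed. The cost is some precision. Ignoring the small extra variance from an arm imbalance in the covariate, the standard error of d2 without the first-class covariate is 1/√(1 − rho²) times as large: 1.05, 1.15 and 1.40 for rho = 0.3, 0.5 and 0.7. For the difference in change the ratio is √(2/(1 + rho)): 1.24, 1.15 and 1.08. The diurnal covariate may recover part of this. The narrower interval given up belongs to a quantity that answers neither question unless d1 = 0.

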#### Treatment allocation

##### Randomization

Participants will be randomly assigned (1:1) to either the 12-month, twice-weekly PRT program or the 12-month, twice-weekly BAT program. The randomization sequence will be generated and held by a central web-based randomization service. Permuted blocks of varying sizes will be used to ensure balance over time.

##### Allocation concealment

Participant recruitment and enrollment will be managed by research personnel who will screen for eligibility, acquire consent, and conduct baseline assessments. Randomization to an intervention group will occur after completion of the baseline assessments. Research personnel conducting assessments and data analysis will be blinded to group allocation so unblinding will not occur. We will not be able to blind participants or personnel delivering the interventions and obtaining the monthly physical activity data (see intervention compliance). Blinding will be supported by providing explicit instructions to the research personnel and participants not to discuss issues related to physical activity during the assessments.

#### Experimental groups

All classes will be led by certified instructors with a participant to instructor ratio of 4:1. Each 60-min class will include a 10-min warm up (i.e., stretching of the major muscles and walking on the spot), 40-min of training, and a 10-min cool down (i.e., stretching and relaxation techniques). Every instructor will be audited on a monthly basis by the exercise class coordinator to ensure consistent protocol delivery.

##### Progressive resistance training

The PRT program will consist of a combination of free weight exercises including mini-squats, mini-lunges, and lunge walks and pressurized air system exercises including biceps curls, seated row, latissimus dorsi pull downs, triceps extension, leg press, hamstring curls, and calf raises. The intensity of training will begin at 50–60% of their 1 repetition maximum (1RM) and progress to 2 sets of 6–8 repetitions at 75–85% 1RM by week 4. The 7RM method will be used to increase the training load when 2 sets of 6–8 repetitions are completed with the correct form. The number of sets completed and the load lifted will be recorded for each participant at each class.

To meet the public health mandates of COVID-19, when it is necessary, training will occur at home, with the use of resistance bands of various weights. Participants will be provided access to instructional videos by either YouTube or DVD. They will be called on a weekly basis to monitor progress and compliance.

##### Balance and tone training

The BAT program will consist of stretching, basic core/kegal exercises, deep breathing, and relaxation techniques. Other than body weight, no additional loading will be applied to any of the exercises. This training has not been shown to improve cognitive function [82] and thus will serve as a control for confounding variables such as physical training received by traveling to the training centers, social interaction, and changes in lifestyle secondary to study participation.

To meet the public health mandates of COVID-19, when it is necessary, training will occur at home, with the use of small equipment (e.g., Pilate ball). Participants will be provided access to instructional videos by either YouTube or DVD. They will be called on a weekly basis to monitor progress and compliance.

#### Intervention compliance

Class attendance will be recorded by the instructors and compliance will be defined as the percentage of the total classes attended. To promote adherence to the exercise program, we will implement strategies including: (1) regular contact; (2) developing coping and action plans; (3) setting implementation intentions and concrete plans; and (4) encouraging participants to self-monitor their progress. Monthly monitoring of extracurricular physical activities will also be performed by an unblinded assessor using the Physical Activities for the Elderly [83, 84] questionnaire throughout the study. In addition, at each measurement point, physical activity over 14 days will be quantified using data acquired by the MW8 [76].

#### Data and adverse event monitoring

A Data and Safety Monitoring Committee will be established by co-investigators who will be independent from the day-to-day conduct of the study. They will review all adverse events on a monthly basis and stop the study if the data are of sufficient concern (e.g., increased rate of falls as a result of the intervention). All adverse events will be reported to this committee and to the relevant university and health authority ethics boards by the study coordinator. There is no anticipated harm and compensation for trial participation.

### Statistical analyses

The analyses will follow the intention-to-treat principle (i.e., all individuals will be analyzed according to their group allocation regardless of compliance). We will evaluate between-group differences (PRT vs. BAT) in ADAS-Cog-Plus and WMH volume, adjusted for baseline score, using mixed linear models. Restricted maximum likelihood estimation will be used in order to include all randomized participants to estimate treatment effects, regardless of loss to follow-up. Time since baseline (6 months versus 12 months) will be considered as a repeated variable and will be included as a fixed effect in addition to group and group-by-time interaction. Baseline score on the outcome variable and participant baseline characteristics will be included as fixed covariates. The intercept will be specified as a random effect. Primary and secondary outcomes will be analyzed using this same analytic model.

The intention-to-treat analysis will be followed by a complete-case analysis, in which only participants with valid data at all time points will be included. Moreover, we will compare participants in the PRT group who are compliant with the intervention (defined as attending at least 60% of the total exercise sessions) with the BAT group.

To explore underlying mechanisms, we will assess the association between changes in cognitive function with changes in: (1) neuroimaging outcomes; (2) cardiometabolic risk factors; (3) blood biomarkers; and (4) saliva biomarkers.

The economic evaluation will examine the efficiency of the 12-month PRT program compared with BAT. The outcome of our cost–utility analysis is the incremental cost–utility ratio (ICUR): ICUR = ∆Cost/∆ quality-adjusted life years (QALYs); QALYs, estimated from the EQ-5D-5L, represent time spent in given health states [85, 86].

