## Methods

### Design

We will conduct a 12-month, parallel group, proof-of-concept RCT of 88 community-dwelling adults with SIVCI, aged 55 years and older. Participants will be randomly assigned to receive 12 months of (1) twice-weekly PRT or (2) twice-weekly balance and tone training (BAT; active control). There will be three measurement points occurring at baseline, 6 months, and 12 months conducted by blinded assessors (Fig. 1). The experienced research team will implement standardized protocols and train study personnel (Fig. 2).

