### Sample size calculation

Power analyses were conducted in G*Power 3.1 [48]. We have sized this trial to allow the evaluation of PRT on the Alzheimer's Disease Assessment Scale-Cognitive-Plus (ADAS-Cog-Plus) [49] and WMH progression at trial completion; WMH progression is considered a valid surrogate marker in therapeutic trials of SIVCI [50]. The ADAS-Cog-Plus is the original ADAS-Cog-13 with additional measures of executive functions and verbal fluency, and it is more sensitive to subtle cognitive changes than the original ADAS-Cog-13 or ADAS-Cog-11 [49]. Our prior 6-month RCT of aerobic exercise on cognitive function, as measured by the ADAS-Cog-11, in adults with SIVCI observed an effect size of 0.89 (Cohen’s *d*) in the complete-case analysis [51]. We also demonstrated twice-weekly PRT slowed WMH progression in older women; the effect size observed was 0.60 (Cohen’s *d*). Based on this effect size of 0.60, assuming an alpha of 0.05 (two-tailed) and a beta of 0.20, 35 participants per group will provide a power of 0.80 [48]. We are aiming to recruit a total of 88 participants with SIVCI (i.e., 44 participants per group), which will accommodate a conservative 20% drop-out rate.

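### Class-based training in both arms could correlate outcomes within class or instructor, but the planned model and the power calculation make no allowance for it

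*Protocol article*

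**What the plan says.** Allocation is to individuals (Randomization): "Participants will be randomly assigned (1:1) to either the 12-month, twice-weekly PRT program or the 12-month, twice-weekly BAT program". Delivery in both arms is by class (Experimental groups): "All classes will be led by certified instructors with a participant to instructor ratio of 4:1". The same section adds a check on delivery: "Every instructor will be audited on a monthly basis by the exercise class coordinator to ensure consistent protocol delivery". Both programmes move to the home when pandemic rules require it; for PRT the text begins "To meet the public health mandates of COVID-19, when it is necessary, training will occur at home, with the use of resistance bands of various", and the BAT section has a parallel provision.

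The Statistical analyses section specifies a linear mixed model with group, time, group-by-time interaction, baseline score and unnamed baseline characteristics as fixed effects. On random effects it says: "The intercept will be specified as a random effect. Primary and secondary outcomes will be analyzed using this same analytic model".

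The Sample size calculation takes d = 0.60, two-tailed alpha 0.05 and beta 0.20, and concludes that "35 participants per group will provide a power of 0.80". It inflates this to 44 per group for 20% drop-out. The article mentions no clustering, ICC, design effect or cluster-robust variance.

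**The concern.** Individual randomisation followed by group treatment creates a level of grouping that did not exist at allocation. People in one class share an instructor, companions and the way sessions are run, so their outcomes may be more alike than those of people in different classes. In a repeated-measures model, a random intercept is naturally read as the participant's own. It handles correlation between one person's visits, not between people.

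If there is positive correlation within class or instructor, the variance of each arm mean is larger than the model assumes. Confidence intervals for PRT versus BAT would then be too narrow and the false-positive rate above 0.05. This would affect both primary outcomes and every secondary outcome, because one model serves them all. Power worked out for independent participants would also be optimistic.

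**Working it through.** **Inputs from the article.** d = 0.60; two-tailed alpha 0.05; 35 evaluable per group; 20% drop-out; 4:1 participant-to-instructor ratio.

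**Assumptions, because the article gives no figure.** Cluster size m = 4, borrowed from the 4:1 ratio, with 9 and 12 for an instructor who sees more participants over the trial. ICC 0.05, range 0.01 to 0.10. Equal clusters in both arms.

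**Step 1: the plan's own figure.** The exact two-sample t-test at 35 per group, d = 0.60 and two-sided 0.05 has power 0.70. Two-sided power of 0.80 needs 45 per group. The stated 35 is matched only by a one-sided test (power 0.7996). The drop-out step does reproduce: 35/0.8 = 43.75, so 44 per group and 88 in total. The two-tailed mismatch is a separate matter; here it only sets the starting power. I use 36 per arm below, because it divides into 9 clusters of 4. Independent power there is 0.709.

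**Step 2: effect on the test level.** Design effect DE = 1 + (m − 1) × ICC. The true standard error is √DE times the model's. The true level of a nominal 0.05 test is 2 × (1 − Φ(1.96/√DE)).

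| m | ICC | DE | √DE | True level |
|---|---|---|---|---|
| any | 0 | 1.00 | 1.000 | 0.050 |
| 4 | 0.01 | 1.03 | 1.015 | 0.053 |
| 4 | 0.05 | 1.15 | 1.072 | 0.068 |
| 4 | 0.10 | 1.30 | 1.140 | 0.086 |
| 9 | 0.05 | 1.40 | 1.183 | 0.098 |
| 12 | 0.05 | 1.55 | 1.245 | 0.115 |

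For m = 4 and ICC 0.05: 1.96/1.072 = 1.828, and 2 × (1 − Φ(1.828)) = 0.068. A simulation with 36 per arm and 40,000 replicates gave 0.065 for the same case.

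**Step 3: effect on power at 36 per arm, m = 4, ICC 0.05.** The noncentrality is 0.60 × √(18/DE).

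- Independent participants, 70 df: 0.60 × √18 = 2.546, power 0.709.
- Correlation added, still 70 df: 0.60 × √(18/1.15) = 2.374, power 0.648. The loss is about 6 points.
- Correlation added, t-test on 18 class means, 16 df: power 0.606. The loss is about 10 points.
- No correlation, t-test on class means, 16 df: power 0.667. About 4 points are lost with nothing to correct.

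So about 6 of the 10 points come from correlation. The rest is the degrees-of-freedom price of analysing class means. These are simple two-sample tests, not the baseline-adjusted mixed model in the plan, so they show the scale of the effect and are not exact operating characteristics.

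**The case against.** The best reply is that the article describes no fixed clusters. The 4:1 figure is a ratio, not a class size; the numbers of classes and instructors are not given, and nothing says participants stay in one class. Enrolment was slow: 69 people from May 2016 to October 2020, roughly 53 months, is about 1.3 a month. With 12 months of training each, that is about 16 people in training at a time, or 8 per arm, so rosters would turn over. Resistance loads are set individually, assessors and the reader of white matter hyperintensities (WMH) are blinded, and home training breaks up the grouping. All of this stands. It makes a small ICC plausible, but does not show that it is zero.

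A reader might infer that the standard errors are too small as a matter of fact. The article does not support that: it needs a positive ICC, which the text neither gives nor implies. A reader might also take the monthly audit as an admission that instructors differ. The text says only that the audit is meant to keep delivery consistent.

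A second reply is that clustering terms belong in an analysis plan not shown here. This carries some weight, since the article condenses the analysis. But it does state a random-effects structure, "The intercept will be specified as a random effect", and applies the model to every outcome. Questioning a stated choice differs from asking for an unseen detail.

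A third reply is that a class effect in the primary model may do harm. The class mainly attended is known only after randomisation and is undefined for people who never attend, while the plan analyses everyone randomised. With few instructors the variance is poorly estimated. This objection succeeds against changing the primary model, but not against a sensitivity analysis.

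**Conclusion.** The point holds conditionally. The design allows correlation within class or instructor in both arms, and neither the stated model nor the sample size allows for it. If such correlation exists, the PRT versus BAT standard errors will be too small.

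At clusters of 4 the inflation is modest: a true level of about 0.053 to 0.086 over ICC 0.01 to 0.10. It becomes material, about 0.10 to 0.12 at ICC 0.05, only if the operative cluster is an instructor with 9 to 12 participants. Home training would lower all of these, and at ICC 0 there is no effect. The power cost due to correlation is about 6 points at ICC 0.05 and clusters of 4; a 10-point loss should not be charged to clustering. Every figure rests on an assumed ICC and cluster size. This justifies a prespecified check, not a new primary analysis.

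**What to change.** In Statistical analyses, keep the planned model as primary. Prespecify a sensitivity analysis, for the primary outcomes and for the secondary outcomes that share the model, that adds a random effect for lead instructor or for the class assigned at randomisation or first scheduled. Either must be defined so that every randomised participant has a value, including those who never attend. Use Kenward-Roger or Satterthwaite degrees of freedom and report the estimated ICC. State in advance that a positive primary result that does not hold in this analysis will be interpreted with caution.

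In Sample size calculation, add a sentence saying that the power figure assumes no correlation within class or instructor.

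The cost is wording, one extra variance term and a grouping variable. Instructors already record attendance (Intervention compliance), so most of the information should be recoverable; the initial assignment of non-attenders would have to come from scheduling records. No extra participants or visits are needed. The downside is slightly wider intervals in the sensitivity analysis and an imprecise variance component if instructors are few.
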